### Population

Adult patients (≥18 years) who were for the first time diagnosed with hyperthyroidism (the list of codes in online supplemental appendix) between 1 January 1996 and 31 December 2015 will be eligible for inclusion. To minimise missed cases, the diagnosis will be additionally identified by a prescription of carbimazole or propylthiouracil, which are ATDs indicated only for treatment of hyperthyroidism. A minimum of 12 months of data must be available before the date of diagnosis and after the index date. CPRD records need to be classified as acceptable research quality.

10.1136/bmjopen-2021-055219.supp1Supplementary data

Exclusion criteria encompass ATD treatment of duration shorter than 6 months as the only treatment, that is, with no radioactive iodine or thyroidectomy followed. This is to avoid contamination by misdiagnosis or spontaneously resolving thyroiditis. Patients treated with both definitive treatment methods, that is, radioiodine and thyroidectomy, will also be excluded. However, ATD treatment followed by either radioiodine or thyroidectomy (one of the definitive treatments) is considered a pretreatment and does not constitute an exclusion criterion.

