### Outcomes

The primary outcome is weight change (in kilogram) during and following the treatment for hyperthyroidism, as well as prevalence of obesity following the treatment. The secondary outcomes include cardiometabolic events and mortality as presented in table 1.

**Table 1 T1:** Secondary outcomes and their data sources

Secondary outcome	Source
MACE (cardiovascular death, nonfatal myocardial infarction or non-fatal stroke)	HES
Type 2 diabetes mellitus	CPRD
Congestive heart failure	HES
Ischaemic heart disease	HES
Stroke and transient ischaemic attack	HES
Cardiovascular mortality	ONS
All-cause mortality	ONS

CPRD, Clinical Practice Research Database; HES, Health Episode Statistics; MACE, major adverse cardiovascular event; ONS, Office for National Statistics.

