### Index date and follow-up

The index date in the cohort is the date of initiation of treatment for hyperthyroidism, which defines the treatment group (either ATD, radioiodine or thyroidectomy). There is a requirement of at least 12 months’ data available prior to the index date.

The natural history of weight changes will be modelled preindex and postindex date. While the follow-up for the analysis of outcomes will start at the index date, a minimum of 12-month follow-up is required for the inclusion.

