The estimation of propensity weights will be conducted by the method proposed by McCaffrey *et al*.^31 32^ The appropriateness of IPW analysis will be assessed by checking the overlap (positivity assumption). According to the positivity assumption, each patient should have a non-zero probability of being indicated to each treatment category. Lack of overlap in the distribution of observed pretreatment characteristics between groups receiving different treatment indicates the positivity assumption is violated. This overlap will be checked visually. If poor overlap is identified, we will use Rubin’s trimming method,^33^ allowing discarding non-overlapping cases.

Further, pairwise balance in the distribution of all included variables between the three treatment groups will be tested with linear regression for continuous variables, logistic regression for binary and multinomial logistic regression for nominal variables. The analysis will be done without and with adjustments. The propensity weights will be considered balanced if there are no statistically significant (p<0.05) differences between the likelihood of receiving a different type of treatment. If imbalances remain after weighting, a doubly robust estimation approach will be applied^32^; that is, the imbalanced variables will be added to the model.

While IPW will adjust for confounding at baseline, other time-varying adjustments will be applied to correct for the events between the baseline and the outcome. The proposed covariates are treatment with levothyroxine for developed hypothyroidism, log TSH levels and informative observations of number of GP visits in a unit of time.

Incidence rate ratios of outcomes will be calculated with Poisson regression and modelled adjusting for time-varying covariates as listed further. Time-to-event analysis with adjustments will be modelled. The appropriate model will be applied, depending on the proportional hazard assumption’s results: if the assumption holds—Cox proportional hazard regression will be used; if it is violated, alternative techniques such as time-varying measures in extended Cox models will be applied.

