Proposed time-varying adjustments for both analyses will include postindex date data, that is, treatment with levothyroxine for developed hypothyroidism, logTSH levels and informative observations of number of GP visits in a unit of time. To allow for the fact that patients may die, a competing risks approach will be adopted for estimating comparative incidences for non-fatal events to allow for the impact of mortality as a competing risk.^22^

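### Inclusion requires 12 months of follow-up after the index date, yet risk time starts at the index date, so year 1 is death-free by construction in the mortality analyses

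*Protocol article*

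**What the plan says.** Three parts of the protocol article bear on this point.

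- **Time zero and inclusion.** Under Index date and follow-up, "The index date in the cohort is the date of initiation of treatment for hyperthyroidism, which defines the treatment group". The same section continues: "While the follow-up for the analysis of outcomes will start at the index date, a minimum of 12-month follow-up is required for the inclusion". Under Population the rule is an eligibility criterion: "A minimum of 12 months of data must be available before the date of diagnosis and after the index date". Neither section says how a patient who dies within 12 months of index is treated.
- **Outcomes.** "The secondary outcomes include cardiometabolic events and mortality as presented in table 1". Table 1 lists all-cause mortality, cardiovascular mortality and "MACE (cardiovascular death, nonfatal myocardial infarction or non-fatal stroke" (a composite with a fatal component), alongside non-fatal outcomes such as type 2 diabetes and heart failure.
- **Analysis.** Under Cardiometabolic risks and mortality, "Incidence rate ratios of outcomes will be calculated with Poisson regression and modelled adjusting for time-varying covariates as listed further". For time to event, "if the assumption holds—Cox proportional hazard regression will be used", with extended Cox models otherwise. Death is also handled as a competing event: "a competing risks approach will be adopted for estimating comparative incidences for non-fatal events to allow for the impact of mortality as a competing risk". No landmark, delayed entry or removal of first-year person-time is stated.

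A related rule appears under Population and Exposure: a patient treated only with ATDs belongs to the medical arm only if that treatment lasted more than six months. The index date of that arm is the start of ATD treatment.

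**The concern.** Entry to the cohort depends on something that happens after time zero, and for the mortality analyses that something is the outcome itself. Deaths in months 0 to 12 are removed from the numerator, while the survivors' first 12 months stay in the denominator. Comparing the risk of death between the three treatments is part of the stated aim, so three things are at stake: the absolute mortality figures, the Poisson mortality rate ratios, and the ability to see any difference between treatments soon after treatment starts.

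Nothing else in the plan repairs this. Propensity weighting balances characteristics at baseline; it does not correct selection on later survival. The competing-risks analysis is for non-fatal events and cannot restore excluded deaths; the competing mortality it uses is itself zero in year 1. The article does speak of interest in an immortal cohort, but only for a sensitivity analysis of weight, so that passage gives no reason for the rule in the mortality analyses.

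**Working it through.** The article gives no mortality rate, event count or follow-up length for this cohort, so there is no planned figure to reproduce. The absence of year-1 deaths follows from the rule alone. Every size below rests on assumed values.

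**1. Logic.** Inclusion requires observed follow-up of at least 12 months after index. An included patient's death time is therefore at least 12 months. Deaths in year 1 are zero, and each included patient contributes one full year of person-time.

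**2. Death rates.** With constant hazard h and mean follow-up F years among included patients, deaths per patient are h × (F − 1), spread over F years. The calculated rate is h × (F − 1)/F, an understatement of 1/F:

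- F = 10: 10%
- F = 9: 11.1%
- F = 6: 16.7%
- F = 5: 20%

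An exponential model with hazards of 0.01 to 0.04 per person-year and maximum follow-up of 3 to 20 years gives rates about 5% to 34% too low. At a hazard of 0.02, the rate counted from index is 0.0132, 0.0159, 0.0178 and 0.0188 for maximum follow-up of 3, 5, 10 and 20 years, against 0.0200 when risk time starts at 12 months.

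**3. Cumulative incidence of death.** At a hazard of 0.02, the 10-year value is 1 − exp(−0.20) = 0.181 for everyone followed from index. In the included cohort it is 1 − exp(−0.18) = 0.165, and the curve is flat for the first year.

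**4. Poisson mortality rate ratio.** With equal true hazards, the calculated ratio is [(F₁ − 1)/F₁] / [(F₂ − 1)/F₂]:

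- 6 versus 9 years: (5/6)/(8/9) = 0.94
- 5 versus 8 years: (4/5)/(7/8) = 0.91
- 7 versus 8 years: (6/7)/(7/8) = 0.98
- equal follow-up: 1.00

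**5. Cox hazard ratio for death.** A simulation of 60,000 patients used a baseline hazard of 0.02 and 10 years of follow-up. One group had three times the hazard in year 1 and the same hazard afterwards. The hazard ratio was 1.21 in the full cohort and 0.99 in the included cohort. The latter was 0.99 whether the clock started at index or at 12 months, because risk sets without events contribute nothing. About 27% of that group's 10-year deaths fell in year 1 and were excluded.

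**6. Non-fatal events.** A heart failure admission at month 4 counts if the patient lives to month 12 and is lost if the patient dies at month 8. Year 1 is therefore not event-free, and the 1/F dilution does not apply. The fault is selection of early events by later survival.

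**7. Dropping the 12-month rule alone.** The six-month ATD rule would remain and would give only the ATD arm guaranteed survival time. With mean ATD follow-up of 9 years, a true rate ratio of 1.00 (definitive treatment versus ATD) becomes 1/(8.5/9) = 1.06; with 8 years it becomes 1/(7.5/8) = 1.07. Unlike the common rule, this would also enter the Cox hazard ratio.

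**The case against.** Several points on the other side have force.

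- **Wording.** The Population section asks for data to be available, which could mean database coverage rather than survival. The other section, however, speaks of follow-up, and no text exempts deaths. If coverage was meant, the text needs to say so.
- **All arms are treated alike.** A reader might infer the familiar bias in which one treatment alone receives immortal time. The documents do not support that: the 12-month rule is common to all three arms. Contrasts are distorted only where follow-up length or early mortality differs.
- **Not every outcome is diluted.** A reader might infer that all rates in Table 1 are biased downwards by 10% to 20%. That holds for fatal outcomes only.
- **Rate-ratio shifts depend on assumptions.** Later index dates after definitive treatment are plausible, because the article treats preceding ATDs as pretreatment. But it gives no interval and no follow-up by arm, and a one-year gap moves the ratio only to 0.98. The arithmetic is also for a simple rate ratio. The Confounding section lists time since diagnosis among its time-varying covariates, which might absorb part of the shift. It is not time since index, however, and the time-varying list for these particular models omits it.
- **Early procedural deaths.** One might infer that the rule hides deaths after surgery or radioiodine. The article gives no early mortality by arm, so this is a possibility only.
- **Secondary outcomes.** Weight and obesity are primary, and long-term risk is a stated interest. That lowers the weight of the point but does not remove it.

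**Conclusion.** The concern holds for fatal outcomes. Read as written, year-1 deaths are excluded while year 1 counts as time at risk. Rates of all-cause mortality, cardiovascular mortality and the fatal part of MACE are therefore understated by about 1/F under a constant hazard (10% at 10 years, 20% at 5 years). Cumulative incidence of death is understated as well. Poisson mortality rate ratios move only if follow-up differs by arm; 0.94 and 0.98 show the range for an assumed three-year and one-year gap.

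It would be tempting to say that the Cox mortality hazard ratios are diluted too. They are not. They answer a narrower question, conditional on 12-month survival, and any earlier difference between arms cannot be seen. Non-fatal outcomes suffer selection, not dilution, and the article offers nothing from which to size it.

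**What to change.** For the cardiometabolic and mortality analyses, start person-time and risk sets at index plus 12 months in all three arms. State that estimates are conditional on 12-month survival. Report year-1 deaths and events by arm among otherwise eligible patients. This also covers the six-month ATD rule. It needs a sentence in the follow-up section and a changed start date in the analysis dataset. The cost is one year of person-time per patient, and with it the year-1 non-fatal events, which would appear only in the descriptive report.

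The landmark removes the dilution but does not bring early deaths into the comparison. If those matter, the 12-month post-index requirement can be dropped and patients followed from index with censoring, but only if the six-month ATD rule is handled at the same time. Two ways to do so are a common six-month landmark, or starting ATD-arm risk time once that rule is met. Otherwise the ATD arm alone would carry immortal time.

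If the requirement was meant as database coverage, the article should say that patients who die within 12 months remain eligible. The six-month ATD rule then needs the same handling.

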### Data analysis

#### Natural history of weight changes

Descriptive statistics will provide summaries about the sample and weight as the outcome measure.

The natural history of weight changes will be modelled longitudinally. The model will estimate the weight (kilogram) over three stages: premorbid, duration of treatment and post-treatment. Premorbid weight is defined as body weight recorded at least 3 months before diagnosis or treatment initiation (whichever comes first). The treatment phase will start from the time of diagnosis or the first prescribed dose or procedure and will last until 3 months after the last recorded date of treatment. Any weight recoded thereafter will be considered as post-treatment.

Only patients having at least one weight record (quantitative or qualitative) in each of the three phases of the condition (premorbid, treatment and post-treatment) will be included in the natural history of weight analysis. The extent of missing data will be reported. As with any real-world data, we anticipate a relatively high proportion of intermittent missing weight data. This missingness can be assumed to be missing at random conditional on other covariates.^20^ Hence, the missing values will be imputed using the multiple imputation by chained equations (MACE).^21^ To improve precision of the imputation, the existing qualitative information from Read codes stating the direction of change (eg, ‘weight increasing (1622.00)’) or body mass index (BMI) status (eg, ‘overweight (22AA.00)’) together with other demographic and clinical covariate data will be entered into the imputation regression model.

Additionally, in order to allow for the fact that patients may die, and their weight trajectories will be subject to informative dropout due to death, we will model weight changes using a flexible joint modelling approach.^22^ Effectively, the analysis of weight history will combine three techniques: (1) complete-case analysis (including only patients with at least one, either quantitative or qualitative, weight status code in each of the phases); (2) imputation of weight where qualitative codes are present; and (3) joint modelling to incorporate the informative missingness due to death. To check the sensitivity of the correctly specified imputation model, a fully Bayesian approach that jointly imputes missing values and estimates the parameters of the longitudinal model will also be conducted.^23–25^ Weight in all three treatment groups will be modelled simultaneously; the ATD group will be used as the reference group. Any marginal pairwise comparisons will be corrected for multiple testing by applying Bonferroni correction.

Further, the sensitivity to death and to missed treatment coding will be checked. During our meetings with the patients, we were informed that weight changes are important but are not of the utmost priority. In the face of death or any serious illness, weight maintenance loses its importance. Hence, our interest in weight changes in an immortal cohort, and thus, we would like to model weight in patients in such health that allows them to survive to the end of the study. Patients who died during the study will be excluded.

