## Introduction

Hyperthyroidism is a common condition affecting 3% of women and 0.3% of men in the UK.^1^ Common clinical features indicating hyperthyroidism include weight loss, heat intolerance, tremor, palpitations and anxiety.^2^ Treatment is critical to minimise complications including atrial fibrillation and stroke that contribute to the observed 20% increase in mortality.^3^

There are three treatment options: antithyroid drugs (ATDs), radioactive iodine (I-131, radioiodine) or surgical, either as a total or hemithyroidectomy. ATDs are associated with a high rate of relapse (30%–70%),^4^ while treatment with radioiodine or thyroidectomy leads to the development of hypothyroidism, requiring lifelong levothyroxine replacement, which is seen in 80% of patients administered radioiodine and up to 100% undergoing thyroidectomy. Guidance recommends discussion of all three options with the patient.^5 6^ There is insufficient evidence to recommend one treatment over the others, although some studies indicate differences in cardiac events and mortality between the treatment modalities.^7 8^

Weight gain following various treatments for hyperthyroidism has been described.^9 10^ Clinicians commonly assume that the observed weight gain is a simple regain of weight lost prior to the initiation of treatment. However, an analysis of 1373 patients with hyperthyroidism has demonstrated a higher prevalence of obesity at 3 years of follow-up when compared with the age-matched and sex-matched background population (37% vs 26% in men, p<0.001; 32% vs 26% in women, p<0.001).^11^ These findings suggest excess weight gain beyond patients’ premorbid weight (weight overshoot). Additionally, the study showed significant differences in final weight gain compared with baseline between those treated with ATDs (5.4 kg, 95% CI 4.8 to 6.0) and those who received radioiodine but did not develop hypothyroidism (5.1 kg, 95% CI 4.3 to 6.1) when compared with those treated with radioiodine who developed subsequent hypothyroidism (7.1 kg, 95% CI 6.6 to 7.7). The extent of weight change in patients treated with thyroidectomy was not evaluated.

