Prior to diagnosis, the majority of patients with hyperthyroidism notice that they lose weight, often despite increased appetite, due to the regulatory effects of thyroid hormones on metabolism. As thyroid hormone levels normalise following treatment, weight change may be observed. While weight gain following treatment is common, it may become a major psychological stressor and can affect treatment compliance. Untreated hyperthyroidism may result in serious consequences, including thyroid storm, heart failure, embolic events, atrial fibrillation, osteoporosis, muscle weakness, neuropsychiatric symptoms and, rarely, cardiovascular collapse and death.^12^ Patients need to be appropriately counselled about the possibility of significant weight gain associated with the treatment of hyperthyroidism. However, there are currently insufficient data available about weight overshoot, cardiovascular risk and treatment modality selection to provide clear guidance to our patients. In our recent survey of British Thyroid Association members, of 35 clinicians who responded, only 23% usually discuss weight gain with patients treated for hyperthyroidism despite 70% of respondents feeling this was a significant clinical problem.

We recently surveyed doctors and dieticians and found that while there was agreement that weight gain following treatment for hyperthyroidism represents a medical problem, there is no consensus about the significance of or the approach to this anticipated weight gain. When surveyed, dieticians expressed concerns that they are not equipped to advise on dietary issues, given the switch from a highly catabolic state (weight loss state) in untreated hyperthyroidism to a situation of anticipated weight gain following treatment.

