### Patient and public involvement

Our patients with hyperthyroidism have been pivotal in formulating the research questions and informing the study design. The study idea originated from listening to patients and their concerns. As part of the consultation process, we held a meeting, advertised locally and nationally via the British Thyroid Foundation (BTF), with patients who had either previously been treated or were currently being treated for hyperthyroidism. During an open discussion, key themes were identified as important to patients across the treatment course of hyperthyroidism. At diagnosis, patients often reported that there was insufficient information to determine which treatment choice would be best for them, particularly regarding long-term treatment consequences; hence, a major driver of the study design is the examination of long-term cardiometabolic outcomes. The comment that “radioactive iodine will make me fat” was repeatedly mentioned in the group discussion. We were already interested in the potential issue of weight gain beyond premorbid weight, and this is something we will be investigating in this project. The main themes reported were that in addition to insufficient information to make a clear, informed treatment choice, patients did not feel that they were suitably counselled about weight regain nor that there was a mechanism in place to predict or modulate this potential effect. The insufficiency of information on the treatment choices and their long-term consequences was further confirmed in a BTF survey involving 353 patients. Among responders who received definitive treatment (n=167) who therefore had knowledge of postdefinitive treatment procedure effects, a third would have not decided to proceed with their choice of treatment.

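### The three weight stages leave out untreated disease, and overshoot may be overstated if weight loss began more than 3 months before diagnosis

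*Protocol article*

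**What the plan says.** All of the definitions stand in the protocol article under Data analysis, Natural history of weight changes.

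- Stages: "The model will estimate the weight (kilogram) over three stages: premorbid, duration of treatment and post-treatment".
- Baseline: "Premorbid weight is defined as body weight recorded at least 3 months before diagnosis or treatment initiation (whichever comes first". No outer limit is set on how old a premorbid record may be.
- Start of treatment stage: "The treatment phase will start from the time of diagnosis or the first prescribed dose or procedure". Unlike the premorbid rule, this sentence does not say which event governs when the two differ. The stage ends 3 months after the last recorded treatment.
- Inclusion: one weight record in each of the three stages is enough.

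The Introduction describes the course before diagnosis: "Prior to diagnosis, the majority of patients with hyperthyroidism notice that they lose weight, often despite increased appetite". It defines overshoot through a cited cohort: "These findings suggest excess weight gain beyond patients’ premorbid weight (weight overshoot". The Patient and public involvement section makes this a question for the study: "We were already interested in the potential issue of weight gain beyond premorbid weight, and this is something we will be investigating in this project". Look-back is set in the Population section: "A minimum of 12 months of data must be available before the date of diagnosis and after the index date".

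**The concern.** By the article's own account the natural history has a phase of loss before any treatment, yet no stage holds it. Weights from that phase are split three ways:

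1. Those 3 months or more before diagnosis or treatment count as premorbid.
2. Those in the last 3 months belong to no stage.
3. Those between diagnosis and first treatment go into the treatment stage if that stage starts at diagnosis. They then share it with weights already regained on therapy. If the stage starts at the first dose or procedure, they have no stage either.

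Overshoot is measured against the premorbid level. If some weights labelled premorbid are already lowered by disease, a patient who only returns to true premorbid weight appears to have gone beyond it. The error has one direction: it inflates overshoot, the quantity on which patients are to be counselled.

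**Working it through.** The article gives no figure on this point, so there is nothing to reproduce. The check is an illustration of possible size.

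**Inputs from the protocol article**
- Premorbid limit: 3 months (Natural history of weight changes).
- Guaranteed look-back: 12 months before diagnosis (Population).
- Minimum records per stage: 1 (Natural history of weight changes).
- For scale, gains in the cited cohort (Introduction): 5.4 kg on antithyroid drugs, 5.1 kg after radioiodine without hypothyroidism, 7.1 kg after radioiodine with hypothyroidism. Differences: 7.1 - 5.4 = 1.7 kg and 7.1 - 5.1 = 2.0 kg.

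**Assumed inputs (not in the article)**
- Weight lost by diagnosis, L: 5 kg, range 3 to 8 kg.
- Time from onset of loss to diagnosis, T: 3, 6 or 12 months.
- Linear loss from onset to diagnosis.

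**Formula.** A weight taken t months before diagnosis is too low by L × max(0, 1 - t/T). If the patient returns exactly to true premorbid weight, this shortfall is the false overshoot.

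**Single record at the 3-month limit, L = 5 kg**
- T = 3: 5 × (1 - 3/3) = 0 kg
- T = 6: 5 × (1 - 3/6) = 2.5 kg
- T = 12: 5 × (1 - 3/12) = 3.75 kg

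**Average over records spread evenly over months 3 to 12, L = 5 kg.** The mean fraction is the integral of (1 - t/T) from 3 to T, divided by 9.
- T = 3: 0 kg
- T = 6: integral 3 - (36 - 9)/12 = 0.75; 0.75/9 = 0.083; × 5 = 0.42 kg
- T = 12: integral 9 - (144 - 9)/24 = 3.375; 3.375/9 = 0.375; × 5 = 1.88 kg

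**Older records included.** Spread evenly over months 3 to 60 with T = 12: 3.375/57 = 0.059; × 5 = about 0.3 kg.

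**Range over L = 3 to 8 kg and T = 3 to 12 months.** Single record at 3 months: 0 to 8 × 0.75 = 6.0 kg. Average over months 3 to 12: 0 to 8 × 0.375 = 3.0 kg.

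**Effect of an earlier cut-off, same assumptions, L = 5 kg.** With records at 6 to 12 months, the average shortfall is 0 for T = 6. For T = 12 it is [6 - (144 - 36)/24]/6 = 1.5/6 = 0.25, or 1.25 kg. With records at least 12 months before diagnosis it is 0 for any T up to 12 months.

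**The case against.** The strongest reply is that the 3-month limit is itself a safeguard. It removes the weights nearest diagnosis, which are the most affected, and if loss began within 3 months there is no leak at all. The article gives neither duration nor amount of loss, so it does not show 3 months to be wrong. This stands, and it makes the baseline problem conditional.

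A reader might infer that the stages make it impossible to separate loss, regain and overshoot. The text does not support that. Weight is to be modelled longitudinally, before and after the index date, with a flexible joint model, and the Confounding section lists thyroid function and time since diagnosis as time-varying covariates. Nothing says that weights are reduced to stage means. Such a model may well show the fall before diagnosis. It would not, however, change which records the stage rule labels premorbid.

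A reader might also infer a false overshoot of at least 1 kg. The calculation does not support a floor above zero, and the upper values require a single premorbid record at the 3-month limit. The cited 1.7 and 2.0 kg differences are only a yardstick, because they are gains from that study's baseline and not from premorbid weight.

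Finally, cut-off sensitivity runs are often left to a fuller document that is not shown. Their absence from the article is therefore not the point. The point is a stage definition that the article does fix.

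**Conclusion.** Two things follow from the text without any assumption. Weights in the last 3 months before diagnosis or treatment have no stage, and the untreated weight at diagnosis can be placed in the treatment stage.

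The third is conditional: overshoot may be overstated if weight loss began more than 3 months before diagnosis. The sizes above rest on assumed linear loss, amount and duration. They run from nothing to values as large as the cited group differences, with dilution where older weights exist. The patients most exposed are those whose only premorbid record lies close to the limit, which the one-record rule and the 12-month look-back both allow.

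The reach is limited. It would be tempting to conclude that the comparison between treatments is biased, but that needs the leak to differ by arm, and the article gives no evidence that it does. The BMI and obesity comparison with the Health Survey for England uses post-treatment values only and is unaffected. This is a cheap improvement to a stated rule, not a demonstrated bias in the primary comparison.

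**What to change.** 1. Add a fourth stage, untreated disease. It runs from 3 months before diagnosis or treatment, whichever comes first, to the first antithyroid treatment of any kind. Start the treatment stage at that first treatment. Do not require a weight in the new stage for inclusion.
2. Report three contrasts separately: loss (premorbid to untreated), regain (untreated to post-treatment) and overshoot (post-treatment minus premorbid).
3. As sensitivity analyses, repeat the overshoot estimate with premorbid weight limited to records at least 6 months, and then at least 12 months, before diagnosis or treatment. For each, also re-run the 3-month definition in the same patients who have such earlier records, so that a change in the estimate is not due to a change in patients.

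This uses data already requested. The cost is fewer patients and less precision in the 6- and 12-month runs, because only 12 months of prior data are guaranteed and some patients will have no eligible record. Moving the start of the treatment stage could also remove a patient whose only treatment-stage weight was taken between diagnosis and first treatment. The number affected should be reported.
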